### Power and sample size estimation

The sample size was estimated by using (mean ± S.D) serum ferritin concentrations (ug/dl) from a randomized trial carried out by Blanco-Rojo, Pérez-Granados [7] in 41 women aged 18–35 years with low iron stores to determine the effect of iron-fortified fruit juice consumption on iron and vitamin D status. At week 8, it was observed that (mean ± S.D) serum ferritin concentrations were significantly higher in the vitamin D group (34.1 ± 14.8 ug/l), compared to 24.8 ± 17.7 ug/l in the placebo group (p < 0.05). In this study, the effect size is calculated by dividing the mean difference (9.3 ng/ml) with the pooled standard deviation (16.29). With an effect size of 0.571, the total sample size will be required in the present study is 50 individuals/group (Power = 0.80, α err prob = 0.05). By considering a 20% drop-out rate, the total sample size required to demonstrate a significant difference in serum ferritin concentrations between the vitamin D group and placebo is estimated to be 120 (60 participants/group). The sample size was estimated using G-Power Software (Version 3.1.7).

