### Study visits and procedures

Upon recruitment, they were subjected to a screening process to determine their plasma ferritin and hemoglobin concentrations to include women with marginally low iron stores [plasma ferritin concentration < 20 μg/l] [22, 23] and non-anemic [hemoglobin concentration > 12 g/dl] [24]. **Fig 1** outlines the timepoint of enrollment, interventions, and assessments of study, which included two main phases. Phase I involved the recruitment and screening phase, where potential participants with marginally low iron stores will be identified and randomized. After that, Phase II or the intervention phase will be conducted where all the eligible participants will be supplemented with either vitamin D3-fortified fruit juice containing 4000 IU (100 mcg) (vitamin D group) or placebo-fruit juice (placebo group) daily for eight weeks.

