#### Phase 1: Recruitment and screening

The prevalence of iron deficiency based on plasma ferritin concentration (< 15 μg/l) in women aged 18–40 years in Malaysia was reported to be approximately 33% [25]. Meanwhile, the prevalence of adult women who consumed vitamin and mineral supplements based on the Malaysian Nutrition Adult Survey (MANS) 2014 was reported to be approximately 32.1% [26]. Considering these data, approximately 736 women would have to be screened to achieve the required sample size. All participants will be provided with a participant information sheet (PIS) and a date for the venous blood collection to ascertain their plasma ferritin and hemoglobin concentrations, to determine their iron stores and hemoglobin levels. Then, they will be provided with a written consent form and will be required to complete a screening questionnaire to ensure the eligibility criteria are met. The screening questionnaire will be used to obtain the participants’ socio-demographic characteristics, including age, ethnicity, religion, educational level, and household income.

During the screening session, 1 ml of venous blood will be collected at the clinical laboratory at the Department of Nutrition, UPM by a trained phlebotomist. The whole blood and plasma sample collected will be used to determine the concentrations of ferritin and hemoglobin. Once the blood analysis results are obtained, participants will be notified via email or phone. Eligible participants with marginally low iron stores and non-anemic will be invited to participate in Phase 2 of the study. On the other hand, those with abnormally high plasma ferritin concentrations (> 150 ug/l) and low hemoglobin concentrations (< 12 g/dl) from the screening will be advised to arrange a check-up with their registered general practitioner and excluded from the study.

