#### Venepuncture procedure and blood sampling

Venepuncture will be performed by a trained phlebotomist (supervised by a medical doctor who is a research team member) to obtain 10 ml of venous blood samples from participants at each clinic session. Both whole blood and plasma obtained from the venepuncture will be utilized in the study analysis. Blood samples were collected in lithium heparin and EDTA blood collection tubes (BD Company, New Jersey, USA) for the various blood biomarker analysis. Whole blood samples will be analyzed immediately after collection to measure full blood counts (FBC). On the other hand, venous blood samples will be centrifuged for 10 minutes (1600 g) at 4°C to obtain plasma samples required for iron and vitamin D biomarkers detection, which will then be aliquot into microcentrifuge tubes and stored at -80°C before analysis. Besides, plasma samples collected at three time-points (baseline, interim and post-intervention) will be used to analyze iron status biomarkers (C-reactive protein, ferritin and hepcidin) and vitamin D metabolism biomarkers (25-OH D) concentrations using commercially available ELISA assay kits specific to different biomarkers.

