### Study outcomes and measures

#### Primary outcomes

Blood samples will be collected at three time points during the 8-week course of the study to determine iron status changes and vitamin D biomarkers. The study’s primary outcome will be ferritin concentration, which has been demonstrated to be well-associated with iron storage in the absence of inflammation [27]. A higher concentration of ferritin may be observed with inflammation despite low iron stores, causing the interpretation to be more complex [27]. Nonetheless, this situation can be controlled by measuring the c-reactive protein (CRP), which is included as part of the biochemical analyses in this study. Meanwhile, the full blood count indices (FBC) will provide the amount of functional iron utilized to produce red blood cells [28]. Besides, a peptide hormone that functions to downregulate iron absorption known as hepcidin [29] is also measured to investigate its mechanistic role in iron metabolism homeostasis following vitamin D administration. Plasma 25(OH)D concentration will be measured to determine the circulating vitamin D.

FBC profiling will be carried out using an automated Beckman Coulter Ac.T diff Hematology Analyzer (Bechman Coulter Inc California, USA) and compared to the normal values/ranges [30]. Reagents used to include Coulter reagents and Coulter rinse shutdown diluent will be obtained from Beckman Coulter Inc, California, USA. Besides, commercially available ELISA assay kits will be utilized to determine the iron and vitamin D biomarkers status by measuring the plasma C-reactive protein (CRP) (R&D Systems Inc, Minneapolis, USA), ferritin (Elabscience Biotechnology Co. Ltd), and hepcidin (R&D Systems Inc, Minneapolis, USA) concentrations for iron biomarkers status. Meanwhile, 25(OH)D (Calbiotech Inc, California, USA) concentration will be determined for vitamin D biomarker status. Readings from the concentrations will be compared to the normal thresholds of the specified blood biomarkers [24, 27, 31, 32]. Each ELISA kit assay will be purchased with quality controls (low, medium, high), including with expected range from similar companies supplying the specified kits. A similar assay for each biomarker will be used for all blood samples collected to account for inter-assay coefficient variations.

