### Data analysis

All statistical analyses will be performed using IBM SPSS Statistic Data Editor Software (Version 21). Kolmogorov-Smirnov tests and histogram will be used to determine the normality of the data, while the descriptive statistics will be used to describe the frequencies and median (range) or mean (standard deviation) for categorical and continuous data, respectively. Meanwhile, baseline and clinical characteristic comparisons between the groups (vitamin D and placebo groups) will be carried out using independent t-test or Mann-Whitney test for continuous data, and Pearson Chi-square or Fisher’s exact test for categorical data. Mean change from baseline to all follow time points of the primary outcomes (plasma ferritin, full blood counts, C-reactive protein, hepcidin and 25(OH)D) will be compared between treatment groups using repeated-measures analysis of variance (ANOVA). Additionally, treatment group, baseline characteristics, sun exposure and dietary intake will be used as fixed factor or covariates in the analysis. The adjusted mean difference with 95% confidence interval and Cohen d will represent the magnitude of the vitamin D effect. A 5% level of significance will be used to determine statistical significance in all analyses. Finally, treatment effects will be assessed using an intention-to-treat strategy. After that, the sensitivity analysis will be conducted with the last observation carried forward assumption for missing data for the primary outcome.

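### Neither pre-treatment ferritin value is named as a covariate in the primary ferritin analysis; naming week-0 and screening ferritin together would gain precision from data already collected

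*Protocol article*

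**What the plan says.** Ferritin is the main endpoint: "The study’s primary outcome will be ferritin concentration" (Primary outcomes).

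It is measured twice before treatment.
- **Screening.** Study visits and procedures describes a "screening process to determine their plasma ferritin and hemoglobin concentrations to include women with marginally low iron stores", with a cut-off of 20 µg/l. Phase 1: Recruitment and screening adds that "The whole blood and plasma sample collected will be used to determine the concentrations of ferritin and hemoglobin". The only uses stated for this value are deciding eligibility and advising women with abnormal results.
- **Week 0.** Venepuncture procedure and blood sampling states that "plasma samples collected at three time-points (baseline, interim and post-intervention) will be used to analyze iron status biomarkers (C-reactive protein, ferritin and hepcidin", among other markers. The week-0 blood is drawn at the visit where the numbered container is handed over (Clinic follow-up visits).

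The Data analysis section compares "Mean change from baseline to all follow time points of the primary outcomes" by repeated-measures ANOVA. On adjustment it says only that "treatment group, baseline characteristics, sun exposure and dietary intake will be used as fixed factor or covariates in the analysis". The baseline characteristics are not listed. The abstract adds an interaction between intervention and time point.

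**The concern.** A change score subtracts one week-0 measurement with full weight, so all of that measurement's biological and assay noise enters the response. Using week-0 ferritin as a covariate lets the data choose the weight. A second pre-treatment value then carries further information about each woman's usual ferritin. Eligibility depends on the screening value, so it exists for every randomised woman.

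The protocol names sun exposure and dietary intake for adjustment but not the two measurements of the outcome itself, which are likely to be its strongest predictors. At stake is the width of the confidence interval for the primary comparison. An open-ended covariate phrase also leaves the choice to be made later, when it ought to be fixed before unblinding.

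**Working it through.** **The plan's own figure.** Power and sample size estimation obtains its effect size by "dividing the mean difference (9.3 ng/ml) with the pooled standard deviation (16.29"): 9.3 / 16.29 = 0.571, as stated ("With an effect size of 0.571"). A two-sided two-sample t-test at 0.05 with 50 per group then has power 0.807, so the stated 50 per group reproduces. The value 16.29 is a pooled SD of unadjusted week-8 ferritin from the cited trial. It involves neither change nor covariates.

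**Closed form without selection.** Let ρ be the correlation between any two ferritin values in the same woman. This is an assumption, as the documents give none. With the variance of one measurement set to 1, the residual variance of a single follow-up visit is:
- raw change from week 0: 2(1 − ρ)
- adjusted for week 0: 1 − ρ²
- adjusted for week 0 and screening: 1 − 2ρ²/(1 + ρ)

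The further cut from screening ferritin, beyond week 0, is ρ²/(1 + ρ)².

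| ρ | Raw change | Week 0 | Week 0 + screening | Further cut from screening | Cut, raw change to both |
|---|---|---|---|---|---|
| 0.3 | 1.40 | 0.91 | 0.862 | 5.3% | 38.5% |
| 0.5 | 1.00 | 0.75 | 0.667 | 11.1% | 33.3% |
| 0.7 | 0.60 | 0.51 | 0.424 | 17.0% | 29.4% |
| 0.8 | 0.40 | 0.36 | 0.289 | 19.8% | 27.8% |

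Example at ρ = 0.7: 1 − 2(0.49)/1.7 = 0.424; 1 − 0.424/0.51 = 17.0%; 1 − 0.424/0.60 = 29.4%. The last two columns have different denominators and do not add.

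**Effect of selection.** The cut-off narrows the range of screening ferritin and so weakens it as a predictor. The share of women below 20 µg/l is not stated. It was taken as 33% to 55%, since Phase 1 reports about 33% below 15 µg/l. Simulating with equal correlation and selection, the further cut from screening ferritin is:

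| ρ | Week 8 alone | Mean of weeks 4 and 8 |
|---|---|---|
| 0.3 | 1.6% to 2.3% | 2.7% to 3.9% |
| 0.5 | 4.1% to 5.5% | 6.4% to 8.5% |
| 0.7 | 8.0% to 10.2% | 12.0% to 14.9% |
| 0.8 | 11.3% to 13.5% | 16.3% to 19.4% |

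On the raw scale with log-normal ferritin, the week-8 figures are about 3% to 4% at ρ = 0.5, 6% to 8% at 0.7 and 8% to 10% at 0.8.

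**Variance-component version with selection.** The assumed inputs are log-ferritin with population median 22 or 30 µg/l, between-woman SD 0.6 or 0.8, within-woman plus assay SD 0.2 to 0.4, extra individual change SD 0 or 0.3, and screening below 20 µg/l. The implied unselected correlation between the two pre-treatment values runs from 0.36/(0.36 + 0.16) = 0.69 to 0.64/(0.64 + 0.04) = 0.94. At week 8:
- raw change to both covariates: residual variance falls by about 12% to 30%
- week 0 alone to both: a further fall of about 5% to 20%
- screening ferritin added to raw change, without week 0: 0%

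The 0% is expected. When all repeat values are equally correlated, screening ferritin predicts week 0 and week 8 equally well, and the prediction cancels in the difference.

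**The case against.** The strongest reply is that nothing here is wrong in the plan. Baseline characteristics is an open list, a condensed article may leave its contents to the analysis plan, and either ferritin value could be on it. That stands. A reader might infer that the plan discards screening ferritin; the text neither includes nor excludes it.

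Second, screening ferritin does nothing for the change-score analysis as written. That also stands, which is why the point concerns the pair of covariates. At lower correlations most of the gain comes from week-0 adjustment.

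Third, the size rests on assumed variance components. That stands too: the documents give neither a within-woman SD nor a repeat correlation, so only a range can be offered.

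Fourth, the two pre-treatment samples may not be comparable. Fasting is stated for the three clinic visits but not for the 1 ml screening draw, and the interval to week 0 is not given. Screening results are needed before randomisation, whereas trial plasma is frozen before analysis, so the batch may differ as well. Any of these lowers the correlation and the gain, but none introduces bias.

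A reader might also carry the variance cut into the sample-size calculation and quote a rise in power or an equivalent number of extra completers. The documents do not support that. The effect size of 0.571 uses the unadjusted week-8 SD, whereas the 5% to 20% is a cut in the variance that remains after week-0 adjustment.

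**Conclusion.** The point holds as a modest, optional gain in efficiency. Two pre-treatment ferritin values exist for every randomised woman, and the primary analysis names neither as a covariate. With an unselected repeat correlation of about 0.7 to 0.94 and selection below 20 µg/l, using both in place of raw change would cut residual variance by about 12% to 30%. Screening ferritin accounts for a further 5% to 20% beyond week-0 adjustment, falling to about 2% to 5% if the correlation is 0.3 to 0.5. These are log-scale, single-visit figures under assumed inputs. No figure for power or sample size follows from them.

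Selection on screening ferritin does not bias the adjusted comparison, because the value predates treatment and the cut-off applies equally to both arms.

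**What to change.** In the Data analysis section, state that the primary ferritin model takes weeks 4 and 8 as the repeated outcomes, with treatment, visit and treatment-by-visit, and with week-0 ferritin and screening ferritin both as fixed baseline covariates. If ferritin is skewed, put the outcome and both covariates on the log scale. Change from baseline can stay as the response: on the same scale, with week-0 ferritin in the model, the treatment estimate is identical. Do not add screening ferritin without week-0 ferritin. Settle this before unblinding, and record the assay, fasting state and date of the screening sample.

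The cost is a revised model statement and one or two degrees of freedom. No new data are needed. The sample-size section needs no change on this account.

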### Ethics and dissemination

The study will be carried out according to the guidelines in the Declaration of Helsinki. All procedures involving human subjects were approved by the UPM Ethics Committee for Research Involving Human Subjects (JKEUPM reference: JKEUPM-2020-033). Participants’ information sheet with a written consent form was obtained, and later it will be explained to them that they are free to withdraw at any time, without excuse. The study protocol was registered and is publicly accessible at ClinicalTrials.gov (trial registry number: NCT04618289 – www.clinicaltrials.gov). All information collected for the study will be kept strictly confidential, anonymized and all participants will be allocated a numerical code. Only the researchers conducting the study will have access to such information, and the data will not be shared with any party without the participants’ consent. Furthermore, the data will be collected at UPM, saved in the university network and will be password protected. Moreover, the blood samples will also be anonymized and stored in a freezer located in the laboratory in the Department of Nutrition, UPM. The findings will be written up for publication in peer-reviewed journals and presented at national or international conferences. No individual from the study will be identified in any subsequent report, presentation, or publication. In addition, participants will be awarded a cash honorarium upon completing the study but will not be reimbursed with any other expenses (including travelling) incurred while participating in the study.

## Discussion

Vitamin D has been shown to play a role in calcium [37] and phosphate homeostasis [38], bone health[39] and other human physiological systems, including cardiovascular, brain, pancreas, muscle and immune system, despite the inconsistent findings [39]. Besides, its potential role has recently been suggested in erythropoiesis, especially in linking hemoglobin and serum 25(OH) concentrations in humans, but with limited evidence [17]. Furthermore, the underlying mechanism behind vitamin D’s effect on iron regulation is poorly understood [40]. Besides, the proposed theory was based on observations reported in studies carried out in patients with disease complication-derived anemia, such as hemodialysis patients [41, 42] or critically ill patients [43]. The proposed theory revolves around vitamin D’s mechanism that affects hepcidin expression, pro-inflammatory cytokine production, and erythropoiesis rate. Erythroid precursor cells are responsible for expressing 1,25(OH)D receptors, which stimulates progenitor cell production and development required in erythropoiesis. Consequently, a compromised concentration of the vitamin D active metabolite, 1,25(OH)D, will then change the rate of erythropoiesis [17, 44]. This active metabolite has also been suggested to improve the responsiveness of patients administered with erythropoiesis-stimulating agent (ESA) in managing anemia by improving erythropoiesis, thus decreasing the use of ESA when supplemented with vitamin D [45]. In addition, the involvement of inflammatory cytokines in the proposed mechanism is particularly related to anemia due to inflammation, mostly in chronic disease patients. The release of inflammatory cytokines leads to increased hepcidin concentration, known for its role as an iron regulator [19]. The use of vitamin D has been shown to decrease hepcidin expression and increase ferroportin to export more iron and ultimately decrease the incidence of anemia [40].

Iron deficiency based on plasma ferritin concentration of < 15 μg/l in women aged 18–40 years in Malaysia was reported to be approximately 33%, and anemia is currently 29.9% in the reproductive-aged women group in the recent national survey. Despite the reduction in anemia incidence as opposed to 34.5% in 2015, anemia remains a public health issue not only in Malaysia but worldwide; therefore, findings from RCTs will be clinically relevant. Despite numerous approaches implemented, including dietary modification, iron fortification and supplementation, iron deficiency and anemia are still prevalent in at-risk groups. Each strategy comes with its advantages and disadvantages. Vitamin D utilization has been recently highlighted as a novel iron absorption enhancer that acts through suppressing hepcidin, the main iron regulator, albeit the paucity of intervention studies, especially RCTs. Previous research was mostly (1) cross-sectional studies that cannot establish a causal-effect relationship, utilizing bolus concentrations of vitamin D or fortified in a food vehicle, (2) carried out in patients, and cannot be generalized to the healthy population, or (3) in vitro studies which cannot be directly extrapolated to humans. To the best of our knowledge, this study will be the first RCT to investigate the utilization of vitamin D-fortified juice, consumed daily as part of the diet to recover the iron status in a healthy pool of Malaysian women with marginally low iron stores. The clinical aspects findings in the present study may be relevant to the recovery of iron status in the iron-deficient population by using vitamin D supplementation in food fortification as a novel iron absorption enhancer in the future. The study also will measure hepcidin concentration which may provide information on the mechanism of vitamin D action on iron recovery status, which was not measured in previous intervention studies. The study is limited by not including a specific measure of adherence for the consumption of fruit juices; however, participants will be required to return the used sachets and food diaries during the interim and post-intervention time points to account for compliance. The study will not measure the circulating 25(OH)D concentrations in blood samples using liquid chromatography-tandem mass spectrometry, which is the reference method to quantify vitamin D active metabolite.
